**2.9 How will the outcome measures be measured at follow-up?**

***Secondary outcomes that will be assessed will include:***

1) The proportion of patients who experience a respiratory exacerbation requiring **intravenous** **or oral antibiotics** over the 24 week trial treatment period.

2) Absolute and relative changes in the forced expiratory volume in one second (FEV1) and forced vital capacity (FVC) over the 24-week treatment period.

3) Changes in disease-specific health-related quality of life over the 24 week study treatment

period as assessed by the CysticFibrosis Questionnaire (CFQ-R)- a disease-specific instrument that measures health-related quality of life for adolescents aged 14-18 and for adults with cysticfibrosis. The CFQ-R has been demonstrated in the European and American CF population to be reliable, valid, and responsive to change, and to correlate with SF-36 scores, pulmonary function, and disease severity. Scores are standardized on a 0 to 100 point scale with higher scores representing better quality of life. For children 6-14 years of age we will use the CysticFibrosis Children Questionnaire (CFQ-UK Children), a modified version of the CFQ-R that has been adapted and validated for use in the pediatric age group.

4) No. of exacerbations that result in hospitalisation over the 24-week treatment period.

5) Total number of hospitalisations (all cause) over the 24-week treatment period.

6) The mean number of exacerbations per patient over the 24 –week period.

7) The time to first exacerbation.

8) Premature discontinuation of study medication, for reasons of adverse effects or lack of

efficacy, as judged by the patient’s physician.

9) Incidence of adverse effects and serious adverse events.

10) Eradication of fungal infection/colonization. Those patients whose sputum is negative for fungal organisms on all 3 occasions at 24, 36 and 48 weeks after randomization will be considered to have had their sputum eradicated of fungus.

All efficacy and safety outcomes listed above will be assessed at 24 weeks, but also at 48 weeks after randomization, to determine if there are any lasting positive or negative carry-over effects of 24 weeks of therapy with itraconazole. Quality of life and pulmonary function will be measured at the time of randomization, and thereafter at 4, 12, 24, and 48 weeks after randomization.

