**2.12/2.13 Compliance and Losses to Follow-up**

The patient’s treating physicians will be instructed not to prescribe anti-fungal antibiotics to enrolled study patients. However, if a patient’s physician insists that the patient must be started on an anti-fungal agent during the study period, then the study medication will be stopped (to avoid potential over-dosage). The patient will continue to be followed for the duration of the study period and results will be analysed according to the intention-to-treat principle. Premature discontinuation of study medication, for reasons of adverse effects or lack of efficacy, will be assessed as a secondary outcome.

Based on previous trials, we expect that 5-10% of participants will prematurely discontinue study medication but continue in the study, and that less than 5% of patients will withdraw from the study and be lost to follow-up. Losses to follow-up are rare in CF trials since patients are all followed in a central CF clinic. For instance, in our combination antibiotic susceptibility trial there were no losses to follow-up despite a 4.5 year study duration47. Patient compliance will be assessed by assessing serum itraconazole levels at 12 and 24 weeks. Patients who have detectable blood levels of itraconazole at 12 and 24 weeks will be judged to have been compliant. Patients who are non-compliant will still be included in the primary intention-to-treat analysis.

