*Principal analysis of the secondary outcome measures:* All secondary outcome measures will be analyzed using an ‘intention to treat’ analysis. Any patients who drop out of the study before the 24 week mark will have measurements of airflow obstruction, dyspnea, and quality-of-life done on the last study visit carried forward for purposes of the analysis (ie. endpoint analysis, with the last observation carried forward). Continuous outcome measures including absolute and percent changes in FEV1 and changes in the scores of the components and the total score of the CysticFibrosis Questionnaire (CFQ-R) will be analysed using multi-variate repeated measures analysis of variance using the SAS Proc Mixed program. This procedure allows us to model the covariance structure of the data and allows for missing observations. Kaplan-Meier survival curves will be used to describe the probability of remaining exacerbation-free in the two treatment arms as a function of time from randomization into the study. The curves will be compared using the log-rank test statistic. Subsequently, Cox proportional hazards modeling will be performed to adjust for other variables that are unbalanced at baseline (such as gender, baseline FEV1, home oxygen use, use of chronic inhaled antibiotics, use of chronic oral antibiotics, use of DNAse, use of hypertonic saline, and co-morbid illnesses) that could potentially affect the time to next exacerbation. The mean number of exacerbations/patient will be calculated using a weighted approach to account for each patient’s duration of follow-up in the trial. The 95% confidence interval and the P value of the rate ratio will be obtained by using Poisson regression analysis models with log transformations of the number of exacerbations and the duration of follow-up.

***Other Considerations:*** P-values will be reported as two-sided. Data will be displayed as proportions and means with 95% confidence intervals or medians with interquartile ranges as appropriate. Likewise, measures of effect, odds ratios (logistic regression) and hazards ratio (Cox proportional hazards) will be presented with 95% confidence intervals.

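### Carrying forward the last FEV1 and quality-of-life values of patients who leave before week 24 removes, for those patients, the mixed model's stated advantage; at the expected loss the effect is small

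*Protocol*

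**What the plan says.** The paragraph on secondary outcomes in Protocol section 2.14 contains two rules.

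- Dropouts: "Any patients who drop out of the study before the 24 week mark will have measurements of airflow obstruction, dyspnea, and quality-of-life" taken from the last study visit and carried forward, described as "ie. endpoint analysis, with the last observation carried forward".
- Model: changes in FEV1 and in CFQ-R scores "will be analysed using multi-variate repeated measures analysis of variance using the SAS Proc Mixed program". The stated reason is: "This procedure allows us to model the covariance structure of the data and allows for missing observations".

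The paragraph names no analysis of these outcomes without the carry-forward, and no sensitivity analysis for it. The carry-forward sentence also covers dyspnea, which is not among the outcomes listed in section 2.9.

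Section 2.9 lists the outcomes as "Absolute and relative changes in the forced expiratory volume in one second (FEV1) and forced vital capacity (FVC) over the 24-week treatment period" and change in CFQ-R, "measured at the time of randomization, and thereafter at 4, 12, 24, and 48 weeks after randomization". Section 1.2 makes lung function and quality of life the secondary objectives.

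Section 2.12/2.13 expects that "less than 5% of patients will withdraw from the study and be lost to follow-up". Separately, it expects that "5-10% of participants will prematurely discontinue study medication but continue in the study".

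**The concern.** A likelihood-based mixed model uses each patient's observed visits and, under missing-at-random, needs no filled-in values. Carrying values forward first takes this away for the patients who leave. The model receives a copy of a week-4 or week-12 value in the week-24 position and treats it as a measurement.

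Two things follow. First, each dropout is assumed to stop changing on leaving. The protocol describes CF lung disease as progressive (section 1.3) and expects the drug's antifungal effect to develop over several months (section 2.6), so that assumption is hard to defend in either arm. Second, the standard error is computed as though nobody had left.

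At stake are the week-24 contrasts for lung function and quality of life, and the subgroup analyses in section 2.15, which follow the same approach.

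**Working it through.** **Figures in the plan.** The protocol gives no figure for this point. Its one computed design figure, the sample size, reproduces: 34% vs 19%, two-sided 0.05, 80% power, with continuity correction, gives 148 per arm; 296 / 0.95² = 327.98, so 328. It concerns the primary outcome only. It is used below as 328 / 2 = 164 per arm.

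**Who is imputed.** Only patients who leave the study before week 24: under 5% by section 2.12/2.13. The 5-10% who stop study drug but stay are still measured and are not imputed.

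**Loss of contrast under linear change (an assumption).** Let an arm's true change at week 24 be β, let a fraction d leave, and let their last visit be at week t. The carried-forward mean is

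β[(1 − d) + d·t/24] = β[1 − d(24 − t)/24].

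With the same d and t in both arms, the fraction of the contrast lost is d(24 − t)/24. At d = 0.05:

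- last visit at week 4: 0.05 × 20/24 = 0.042, about 4%;
- last visit at week 12: 0.05 × 12/24 = 0.025, or 2.5%.

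A patient who left before the week-4 visit would carry the baseline value; if all did, the loss would be 0.05 × 24/24 = 5%.

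**Simulation.** 164 per arm, visits at weeks 4, 12 and 24, 1000 runs per case. An unstructured likelihood model was fitted to the filled data and to the observed data. The protocol gives no SD, correlation or trajectory, so these are assumed: SD of change 1, correlations 0.6-0.7, placebo means −0.10, −0.25, −0.50 and active means 0, −0.05, −0.10 (true week-24 difference 0.40 SD). Half of the dropouts leave after week 4 and half after week 12. Cases with more than 5% loss in an arm go beyond what the protocol expects and show only how the effect grows.

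Expected bias at 5% loss in both arms:
- active: 0.025 × 0.10 + 0.025 × 0.05 = 0.00375;
- placebo: 0.025 × 0.40 + 0.025 × 0.25 = 0.01625;
- difference: −0.0125 SD.

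| Case | Expected LOCF bias (SD) | Simulated bias, LOCF / observed | Mean SE, LOCF / observed | 95% CI non-coverage, LOCF / observed |
|---|---|---|---|---|
| 5% both arms, same trajectory | 0 | 0.0005 / 0.0002 | 0.1103 / 0.1116 | 4.3% / 4.3% |
| 5% both arms, difference 0.40 | −0.0125 | −0.0090 / 0.0029 | 0.1105 / 0.1120 | 4.6% / 4.6% |
| 10% both arms, difference 0.40 | −0.025 | −0.0214 / 0.0039 | 0.1105 / 0.1134 | 5.7% / 4.8% |
| 20% both arms, difference 0.40 | −0.050 | −0.0464 / 0.0021 | 0.1107 / 0.1172 | 6.9% / 4.9% |
| 2% vs 8%, no true difference | 0.0195 | 0.0143 / −0.0041 | 0.1109 / 0.1122 | 5.1% / 4.4% |

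Simulation error in the bias is about 0.1076/√1000 = 0.003 SD.

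**Standard error.** With nobody lost it would be √(2/164) = 0.1104. The LOCF value stays there whatever the loss. Against the observed-data model it is smaller by 1 − 0.1105/0.1120 = 1.3% at 5% loss, 2.6% at 10% and 5.5% at 20%.

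**The case against.** The strongest defence is scale. Section 2.12/2.13 expects few losses and reports none in the group's previous trial, so little would be imputed. That stands, and it limits the size of the point.

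A second defence is that the two sentences do not strictly contradict each other. The carry-forward covers only patients who leave before week 24. Visits missed by patients who stay, and losses between weeks 24 and 48, lie outside it, so the model's tolerance of missing data still has a use. That also stands. A reader might infer that nothing is missing after the carry-forward; the text does not go that far. The advantage is lost for dropouts only.

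A third defence is that the endpoint analysis is a separate last-value analysis. The paragraph does not separate it from the mixed model, and Proc Mixed is the only analysis it names for FEV1 and CFQ-R. If two analyses are meant, the text needs to say so.

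Three stronger readings are tempting but unsupported:

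- *That the results will be biased.* With equal dropout and the same trajectory in both arms, the bias was about zero.
- *That the standard error is wrong in itself.* The LOCF standard error roughly matched the spread of the LOCF estimates (0.1105 against 0.1076 at 5% loss). It is too small only relative to a valid analysis of the observed data.
- *That the active arm will lose more patients through adverse effects.* Section 2.18 stops study drug for laboratory toxicity, and section 2.12/2.13 expects patients who stop drug to remain in the study. Unequal dropout is possible, but the protocol does not predict it.

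**Conclusion.** The point holds for the continuous secondary outcomes. Carrying values forward is the only named handling of dropout, it undercuts the planned model for exactly those patients, and a better method is already in the same paragraph.

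At 5% loss, the upper end of what the protocol expects, the effect is small: about 2.5% to 4% of the week-24 contrast under linear change with dropout after week 12 or week 4. In the simulated case it was about 0.01 SD of bias and about 1% in the standard error, with no visible effect on coverage. These figures rest on the assumed SD, correlations and trajectories. The effect grows with higher loss and can arise without any drug effect if dropout differs between arms.

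The primary Fisher's exact comparison and the sample size of 328 are untouched. This is worth correcting, but it does not threaten the trial's main conclusion.

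**What to change.** In section 2.14, delete the carry-forward sentence as it applies to airflow and quality-of-life measures. State that the planned mixed model is fitted by likelihood to all observed visits through week 24, with no filled-in values, and that the week-24 treatment contrast is reported under missing-at-random. Further model terms can be left to the statistical analysis plan.

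If a check on that assumption is wanted, a sensitivity analysis for departures from missing-at-random may take the place of the carry-forward.

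The main change is one of wording: no new data, visits or patients, and no change to the sample size. The optional sensitivity analysis adds a little analysis work.

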**2.14 Statistical Analysis**

*Principal Analysis of the Primary Outcome Measure:*

The final analysis will be performed with an ‘intention to treat’ approach. Patients will be included in the analysis according to the group to which they were randomized regardless of cross-over or compliance. Baseline characteristics of patients in the two treatment arms will be assessed using frequency distributions and univariate descriptive statistics including measures of central tendency and dispersion.

The principal analysis of the exacerbation proportions in the two treatment groups will be conducted using an unadjusted Fishers exact test comparing the proportion of events in the two treatment groups. A logistic regression procedure will be employed to adjust raw exacerbation proportions using important covariates that may be unbalanced at baseline that may influence outcomes (such as gender, baseline FEV1, home oxygen use, use of chronic inhaled antibiotics, use of chronic oral antibiotics, use of DNAse, use of hypertonic saline, and co-morbid illnesses).

We chose the proportion of patients having at least one exacerbation as a primary outcome measure rather than survival time to exacerbation. We believe that it is more clinically relevant to both patients and physicians to know whether or not a patient exacerbates rather than when they exacerbate. Therefore, an analysis of raw proportions followed by logistic regression procedures were chosen over log-rank tests followed by Cox proportional hazards modelling. Both alternative analytic approaches mentioned will be performed and reported.

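### The Proc Mixed analysis of change in FEV1 and CFQ-R names no baseline covariate; section 2.14 should prespecify one

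*Protocol*

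**What the plan says.** Protocol section 2.14, on secondary outcomes, sets the dependent variables as "Continuous outcome measures including absolute and percent changes in FEV1", together with change in the CFQ-R, both by component and in total. It states that these "will be analysed using multi-variate repeated measures analysis of variance using the SAS Proc Mixed program". The sentence lists no fixed effects and no covariate.

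Section 2.9 defines the lung-function outcome as "Absolute and relative changes in the forced expiratory volume in one second (FEV1) and forced vital capacity (FVC) over the 24-week treatment period". FVC is not named in the modelling sentence of 2.14, but as a continuous outcome it falls under the same description.

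Baseline FEV1 appears in two other models of section 2.14. The logistic model for the primary outcome adjusts for "important covariates that may be unbalanced at baseline that may influence outcomes (such as gender, baseline FEV1" and further items. For time to exacerbation, "Cox proportional hazards modeling will be performed to adjust for other variables that are unbalanced at baseline (such as gender, baseline FEV1, home oxygen use" and further items. In both places adjustment is tied to imbalance.

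The baseline values will be available. Section 2.9 states: "Quality of life and pulmonary function will be measured at the time of randomization, and thereafter at 4, 12, 24, and 48 weeks" after randomization.

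**The concern.** Lung function and quality of life are the two secondary objectives in section 1.2. An analysis of change with no baseline term fixes the coefficient of baseline at 1. Where the correlation between baseline and follow-up is below 1, that over-corrects. Patients with a low baseline tend to rise and those with a high baseline tend to fall, in either arm. This has two consequences. The interval for the treatment difference is wider than the data require. And if the arms differ at baseline by chance, regression to the mean moves the estimated difference in change.

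The design does little to limit such a difference. Section 2.3 stratifies randomization by site only, while section 2.5 admits anyone aged 6 or older who weighs at least 20 kg. If the rule of the logistic and Cox models (adjust for what is unbalanced) were carried over to the continuous outcomes, whether to adjust would depend on the data observed.

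**Working it through.** **The plan's own figures.** The protocol gives no SD, target difference, power or correlation for FEV1, FVC or CFQ-R, so there is no figure of its own to reproduce for this analysis. Its only sample-size calculation concerns the binary primary outcome (section 2.10) and does reproduce. With 34% versus 19%, two-sided alpha 0.05, power 0.80 and a continuity correction, the result is 148 per arm, 296 in total; 296/(0.95 × 0.95) = 327.98, that is 328. None of this depends on how FEV1 is modelled.

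**Precision at one follow-up visit.** Assume the same SD, s, at baseline and follow-up and a correlation rho between them.

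- Variance of the change score: 2(1 − rho)s².
- Residual variance after adjustment for baseline: (1 − rho²)s².
- Ratio, adjusted to unadjusted: (1 − rho²)/[2(1 − rho)] = (1 + rho)/2.

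The protocol does not give rho, so the values below are assumptions. The power column takes a difference that the unadjusted comparison would detect with 80% power.

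| rho (assumed) | Variance ratio | Variance removed | Interval narrower by | Power, from 80% to |
|---|---|---|---|---|
| 0.5 | 0.75 | 25% | 13.4% | 89.9% |
| 0.6 | 0.80 | 20% | 10.6% | 87.9% |
| 0.7 | 0.85 | 15% | 7.8% | 86.0% |
| 0.8 | 0.90 | 10% | 5.1% | 84.0% |
| 0.9 | 0.95 | 5% | 2.5% | 82.0% |

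**Precision averaged over the three on-treatment visits (weeks 4, 12 and 24).** Assume the same correlation between every pair of visits. The mean of three visits has variance v = (1 + 2·rho)/3 in units of s². The unadjusted variance is v + 1 − 2·rho and the adjusted variance is v − rho².

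- rho 0.5: v = 0.667; 0.417/0.667 = 0.625.
- rho 0.9: v = 0.933; 0.1233/0.1333 = 0.925.

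For this summary the gain is somewhat larger than in the table.

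**Effect of a chance baseline difference.** Given a baseline difference d between arms, the unadjusted difference in change is shifted by −(1 − rho)d. If d equals 1.96 of its own standard errors, the size of the shift, in standard errors of the change-score estimate, is 1.96 × (1 − rho)/√[2(1 − rho)] = 1.96 × √[(1 − rho)/2].

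- rho 0.5: 1.96 × 0.500 = 0.98.
- rho 0.8: 1.96 × 0.316 = 0.62.
- rho 0.9: 1.96 × 0.224 = 0.44.

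**Percent change.** The formula above covers absolute change only. A simulation of percent change (148 per arm, assumed baseline mean 62 and SD 20, rho 0.8 to 0.95) gave a standard error about 1% to 4% smaller with adjustment.

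**The case against.** The strongest objection is that the omission is read from silence. The sentence in 2.14 lists no fixed effects at all, not even treatment or visit, and nobody would conclude that treatment is left out. Proc Mixed can carry a baseline term, and covariates of a secondary model are often settled in the statistical analysis plan, which is not shown. The lists in the logistic and Cox models concern exacerbations and exclude nothing from the model for FEV1. This stands to the extent that one cannot say the protocol leaves baseline out; one can say only that it names none. The point survives because the protocol itself fixes the outcome as change and the method as repeated-measures analysis of variance, and states its adjustment where it intends one. Followed as written, the result is the less precise analysis, and the better one costs nothing.

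A second objection is size. If rho for FEV1 is about 0.9, the gain is about 5% of variance and 2.5% of interval width. That also stands. The gain would be larger for CFQ-R if its correlation is lower, but the protocol gives neither value.

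A reader might also infer that percent change in FEV1 is a wrong endpoint because small baselines inflate it. The protocol does not support treating that as an error. It specifies absolute as well as relative change, a relative measure is a recognised way to handle differences in body size, and an analysis of log FEV1 would be relative too.

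**Conclusion.** The point holds as a free improvement to the wording of section 2.14. The model for change in FEV1 and CFQ-R names no baseline covariate, although the baseline value is scheduled at randomization. With equal variances and a single follow-up visit, adjustment removes about 25% of the variance at an assumed rho of 0.5 and about 5% at 0.9. The protocol's data cannot narrow that range.

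Two stronger readings should be avoided. First, a reader might infer that the planned comparison is biased. Under randomization it is unbiased with a valid type I error; the shift shown above is conditional on a baseline difference having occurred by chance. Second, a reader might convert the gain into patients saved out of 328. That number was set by the exacerbation proportions, and the correlation needed for the conversion is not given. Fisher's exact test on the primary outcome and the sample size are untouched.

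**What to change.** Add to section 2.14 that the Proc Mixed models for FEV1, FVC and CFQ-R include the baseline value of the same measure, and its interaction with visit, as prespecified covariates, whether or not baseline turns out to be unbalanced. If an analysis plan already says this, a matching sentence in the protocol is enough. The cost is wording only: no extra measurement, visit or patient is needed.

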Of the 61 pediatric patients from the Toronto clinic who were chronically infected with aspergillus, 23% experienced at least one exacerbation during the first six months of 2005 requiring IV antibiotics. In contrast, only 9% of 142 pediatric patients in Toronto who did not culture aspergillus from their sputum had a pulmonary exacerbation during the first six months of 2005 (p < 0.01). Thus it appears from pediatric and adult data that the risk of pulmonary exacerbation is approximately two to three times higher in Canadian CF patients who are chronically infected with aspergillus compared to those who are not. Chronic infection with aspergillus may be associated with increased risk of exacerbations, either because A. fumigatus is a pathogenic organisms that directly causes exacerbations, or because chronic aspergillus infection is associated with sicker patients who are more predisposed to exacerbations.

Data from the Australian CF Registry is similar to Canadian data. 65.9% of Australian pediatric patients who were chronically infected with aspergillus were hospitalized for a respiratory exacerbation in 2003, compared to a pediatric hospitalization rate of 34.5% in those who were not aspergillus-infected (p < 0.0001). Similarly, 61.7% of Australian adults who were chronically infected with aspergillus were hospitalized for a respiratory exacerbation in 2003, compared to an adult hospitalization rate of 44.0% in those who were not aspergillus-infected (p = 0.04). In total Australians with chronic aspergillus infection had 1.23 (sd 1.44) admissions for IV antibiotics per patient-year in 2003 compared with patients who were not infected with aspergillus who had 0.74 (sd 1.25) admissions per patient-year. This corresponds to a risk ratio of 1.66, indicating that Australian CF patients who were infected with aspergillus were much more likely to require hospital admission for pulmonary exacerbations.

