**2.10 Sample Size Calculations:**

The primary outcome measure will be the proportion of patients who experience a respiratory exacerbation requiring intravenous antibiotics in the two treatment groups over the 24 week trial observation period. In our combination antibiotic susceptibility trial we enrolled and followed 251 patients with cystic fibrosis and randomized patients when they experienced a pulmonary exacerbation. Eighty-seven patients (35%) experienced an exacerbation requiring intravenous antibiotics within 24 weeks of enrolment47. Similarly, 32% of placebo-treated patients in The Australian hypertonic saline trial experienced a CF exacerbation requiring intravenous antibiotics within 24 weeks48. Finally, in the TOBI study 100 of 258 actively-treated patients (39%), and 135 of 262 placebo-treated patients (52%) experienced at least one pulmonary exacerbation requiring intravenous antibiotics over the 24-week trial49.

Additionally, data from the 2005 Toronto CF Data Registry suggests that of Canadian adult and pediatric patients who are chronically infected with aspergillus, 27% experienced at least one respiratory exacerbation during the first six months of 2005 which required hospital admission and/or home intravenous antibiotic therapy. According to the statistician ([name]) who administers the database this is likely an under-estimation of the true rate of exacerbations, since data on hospitalizations or home IV therapy can be missing or incomplete within the database.

Thus, based on data from the above-mentioned three recently completed studies, and based on the Toronto database data, we conservatively expect that 34% of placebo-treated patients in our trial will experience a pulmonary exacerbation requiring intravenous antibiotics over the 24 week duration of our trial. The Trial Investigators (4 Canadian CF physicians and 4 Australian CF physicians) determined that a 15% absolute difference in 24-week exacerbation rates between the two treatment groups would be the minimal clinically significant difference that would be important for the study to detect.

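### Plain Poisson regression for the exacerbation rate ratio (secondary outcome 6) ignores the overdispersion in the protocol's own registry figures, so its confidence interval will be too narrow

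*Protocol*

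**What the plan says.** Secondary outcome 6 in protocol section 2.9 is an average count for the on-treatment phase ("The mean number of exacerbations per patient over the 24" weeks). Section 2.9 also has every listed outcome assessed again at 48 weeks.

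Section 2.14 fixes how the comparison is made. Both the interval and the P value for the ratio of rates are to come from one method, described as "Poisson regression analysis models with log transformations of the number of exacerbations and the duration of follow-up". It names no dispersion parameter, robust variance or negative binomial alternative.

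The background subsection on pulmonary exacerbations in patients infected with *A. fumigatus* gives Australian registry figures. Patients with chronic Aspergillus infection "had 1.23 (sd 1.44) admissions for IV antibiotics per patient-year in 2003", and those without it "had 0.74 (sd 1.25) admissions per patient-year".

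Section 2.10 expects that "34% of placebo-treated patients in our trial will experience a pulmonary exacerbation requiring intravenous antibiotics" over 24 weeks, and targets an absolute reduction of 15 percentage points.

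**The concern.** A Poisson model takes its standard errors from the mean alone. When patients differ in their underlying exacerbation rate, counts vary more than the mean implies. The model then understates the uncertainty of the rate ratio: the interval is too narrow and the P value too small. The protocol reports a mean and SD that show this pattern in the kind of patient it will enrol, yet names the model that assumes the pattern away.

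What is at stake is a false claim of fewer exacerbations on a clinically prominent secondary outcome, possibly alongside a primary test that shows no difference. The same approach carries over to the 48-week assessment and to the three subgroup analyses in section 2.15.

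A smaller point concerns the wording. In Poisson regression the count is left untransformed; the log applies to its expected value (the link) and to follow-up time (the offset). The sentence instead puts the log on the number of exacerbations, and the log of zero does not exist.

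**Working it through.** **Inputs.** Infected registry patients: mean m = 1.23, SD 1.44 per patient-year. Uninfected: m = 0.74, SD 1.25 (both from the background subsection on exacerbations). Placebo proportion with an IV-treated exacerbation by 24 weeks: 34%, with a 15-point reduction (section 2.10). Sample size: 328, or 164 per arm (section 2.10).

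**The plan's own figures.** 1.23 / 0.74 = 1.66, which matches "This corresponds to a risk ratio of 1.66". The sample size also reproduces: a continuity-corrected comparison of 34% with 19% needs 148 per arm, and 296 / 0.95² = 328. No power is stated for the rate analysis.

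**Step 1, dispersion in the registry data.** Poisson requires variance / mean = 1.
- Infected: 1.44² = 2.07; 2.07 / 1.23 = 1.69.
- Uninfected: 1.25² = 1.56; 1.56 / 0.74 = 2.11.

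**Step 2, scaling to the trial's periods (assumption: gamma-Poisson).** With k = (SD² − m) / m², the variance-to-mean ratio over a period of t years is φ = 1 + k·m·t. For infected patients, k = (2.0736 − 1.23) / 1.23² = 0.558. The Poisson standard error is too small by √φ, and the two-sided type I error is 2·[1 − Φ(1.96/√φ)].

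| Basis | φ | √φ | Type I error, formula | Simulated |
|---|---|---|---|---|
| Infected registry, 24 weeks (m·t = 0.568) | 1.32 | 1.15 | 8.8% | 8.6% |
| Infected registry, 48 weeks (m·t = 1.135) | 1.63 | 1.28 | 12.5% | 12.4% |
| 34% placebo proportion with k = 0.558, 24 weeks | 1.26 | 1.12 | 8.1% | 7.9% |

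In the third row the mean is solved from the zero proportion: (0.66^(−k) − 1) / k = 0.468. The simulations used 200,000 null trials with 164 patients per arm. A nominal 95% interval covers about 91% at 24 weeks and 87% at 48 weeks on the infected figures.

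**Step 3, a check of the model against other figures in the document.** The same subsection gives the share of patients hospitalised for a respiratory exacerbation in 2003: 61.7% of infected adults and 65.9% of infected children; 44.0% and 34.5% of uninfected adults and children. From the quoted means, Poisson predicts 70.8% (infected) and 52.3% (uninfected), above every observed figure. The gamma-Poisson model predicts 60.8% and 39.2%, close to or within the observed ranges. The two measures (hospitalisation for exacerbation and admission for IV antibiotics) are near but not identical, so this is support and not proof.

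**Step 4, zero counts.** Expected share with no IV-treated exacerbation: 1 − 0.34 = 66% on placebo and 1 − 0.19 = 81% on itraconazole, so 164 × (0.66 + 0.81) ≈ 241 of 328 patients. Counting oral-treated episodes would lower this.

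**The case against.** **The log wording is probably shorthand.** A log link and a log follow-up offset are the two places where logs enter a Poisson model, and the sentence mentions two logs. A reader might infer that the analysis as planned cannot be computed for most patients. The document does not support that: a model called Poisson regression almost certainly has a log link, which handles zeros. Taken literally, the method would fail at once and would not give a wrong answer unnoticed. What stands is a wording correction.

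**The registry data are a proxy.** They are annual Australian admissions for IV antibiotics, not adjudicated exacerbations. The trial requires clinical stability and excludes *B. cepacia* complex and transplant patients, so the spread between patients may differ. This stands against the precision of the size. It gives no reason to expect the spread to vanish.

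**The choice of dispersion correction is often left to the analysis plan, which is not shown.** Silence on that detail would not be a finding. But the protocol goes further: it names the model and makes it the source of the interval and P value, against its own data.

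**The consequence is limited.** This is one of ten secondary outcomes, and the Fisher, logistic, log-rank and Cox analyses do not depend on it. That stands.

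**Conclusion.** The point holds for secondary outcome 6. Following section 2.14 as written, the standard error of the log rate ratio would be too small by a factor of about 1.12 to 1.15 at 24 weeks (type I error about 8-9%) and about 1.28 at 48 weeks (about 12%). The direction follows from the protocol's own mean and SD, provided the excess variance reflects differences between patients observed for about a year each. The size also rests on gamma-Poisson scaling and on trial patients resembling the infected registry patients.

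Three stronger readings are not supported:
- A reader might infer that false positives become two to three times as frequent as intended. At 24 weeks, the period that defines the outcome, the multiple is about 1.6 to 1.8 (8.1/5 to 8.8/5). A higher 24-week figure (11%) needs the dispersion of uninfected patients, whom this trial does not enrol; otherwise the larger multiples belong to the 48-week assessment.
- A reader might infer that the rate ratio itself is biased. Overdispersion leaves the Poisson point estimate consistent; only the standard error, interval and P value are wrong.
- A reader might extend the fault to the hospitalisation counts (outcomes 4 and 5). Section 2.14 ties the Poisson model only to exacerbations per patient and states no model for those two.

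The primary analysis and the sample size are untouched.

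**What to change.** Replace the sentence in section 2.14 with one to this effect: *the rate ratio, its 95% confidence interval and P value will come from negative binomial regression (or Poisson regression with robust standard errors) of the untransformed number of exacerbations, with a log link and log(follow-up time) as offset.* This settles both the overdispersion and the log wording. If outcomes 4 and 5 are analysed as rates, use the same model for them.

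The cost is one sentence and no extra patients or data. The standard error that is reported grows by roughly 12-15% at 24 weeks and 28% at 48 weeks under the assumptions above, so the intervals are somewhat wider. In a simulation of 20,000 null trials on the infected-patient figures, robust variance brought the type I error back to 4.9% at 24 weeks and 5.0% at 48 weeks.
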